## Abstract

**Background:**

The increase of the proportion of elderly people has implications for health care services. Advances in oral health care and treatment have resulted in a reduced number of edentulous individuals. An increasing number of dentate elderly people have tooth wear, periodontal disease, oral implants, and sophisticated restorations and prostheses. Hence, they are in need of both preventive and curative oral health care continuously. Weakened oral health due to neglect of self care and professional care and due to reduced oral health care utilization is already present when elderly people are still community-dwelling. At the moment of (residential) care home admittance, many elderly people are in need of oral health care urgently. The key factor in realizing and maintaining good oral health is daily oral hygiene care. For proper daily oral hygiene care, many residents are dependent on nurses and nurse aides. In 2007, the Dutch guideline "Oral health care in (residential) care homes for elderly people" was developed. Previous implementation research studies have revealed that implementation of a guideline is very complicated. The overall aim of this study is to compare a supervised versus a non-supervised implementation of the guideline in The Netherlands and Flanders (Belgium).

**Methods/Design:**

The study is a cluster randomized intervention trial with an institution as unit of randomization. A random sample of 12 (residential) care homes accommodating somatic as well as psycho-geriatric residents in The Netherlands as well as in Flanders (Belgium) are randomly allocated to an intervention or control group. Representative samples of 30 residents in each of the 24 (residential) care homes are monitored during a 6-months period. The intervention consists of supervised implementation of the guideline and a daily oral health care protocol. Primary outcome variable is the oral hygiene level of the participating residents. To determine the stimulating or inhibiting factors of the implementation project and the nurses' and nurse aides' compliance and perceived barriers, a process evaluation is carried out.

**Discussion:**

The method of cluster randomization may result in a random effect and cluster selection bias, which has to be taken into account when analyzing and interpreting the results.

**Trial registration:**

Current Controlled Trials ISRCTN86156614

## Background

The international literature shows that the proportion of elderly people has increased considerably during the last decades and is expected to further increase during the next decades. This demographic shift will have important implications for health care services. More (frail) elderly people will present more morbidity and care dependency and, consequently, will need an increasing proportion of health care services [1]. Those elderly people, who are not able to function independently, are often supported by domiciliary care service or admitted to (residential) care homes [2,3].

Advances in oral health care and treatment during the last decades have resulted in a reduced number of edentulous individuals. A still increasing number of dentate elderly people have tooth wear, periodontal disease, oral implants, and sophisticated tooth- and implant-supported restorations and prostheses. Hence, they are in need of both preventive and curative oral health care continuously. Complexity of the oral conditions, oral mucosal lesions, systemic diseases, and medication use make (frail) elderly people more vulnerable to oral problems than younger age groups, especially when they are cognitively impaired [4,5]. Weakened oral health due to neglect of self care and professional care and due to reduced oral health care utilization is already present when (cognitively impaired) elderly people are still community-dwelling [5-8]. At the moment of (residential) care home admittance, many elderly people in countries all over the world are in need of oral health care urgently. If their needs are not met, their oral health will be persistently poor and will utmost probably further deteriorate during their residency because of increasing care dependency and subsequent lack of adequate oral health care [9-14].

Systemic diseases affect oral health and vice versa [15,16]. Several medications have also a negative effect on oral health by inducing xerostomia, hyposalivation, mucosal lesions, and abnormal bleeding [17]. Hyposalivation is a specific problem because saliva plays a major role in protecting both hard and soft oral tissues [18]. Furthermore, several aspects of oral health are affecting quality of life and well-being [19-21]. Oral health influences mastication, food selection, weight, speech, taste, hydration, appearance, and psycho-social behaviour and is thereby a concern not only for the elderly individuals themselves, but also for their relatives and care providers [22-25].

The key factor in realizing and maintaining good oral health is daily oral hygiene care by removing the oral bacterial plaque, mainly composed of pathogenic gram-negative germs [26,27]. However, many residents of residential care homes and long-term care facilities are not able to clean their mouths and eventually removable dentures themselves. For proper daily oral hygiene care, they are dependent on nurses and nurse aides [28,29]. However, the importance of oral health of residents is often misunderstood and neglected by nurses and nurse aides [30]. A lack of oral health knowledge and oral health care skills of even qualified nurses is an important inhibiting factor in achieving an acceptable level of residents' oral hygiene [31]. No prioritisation to oral health care of the residents themselves and their family is another barrier of proper oral health and daily oral hygiene care [32,33]. Furthermore, in many cases a resident's repeated resistiveness is disincentive for nurses and nurse aides, leading to inadequate daily oral hygiene care [34]. Teaching and qualifying nurses and nurse aides in providing individual oral health care for residents had until recently a low priority in managers and physicians of residential care homes and long-term care facilities [35,36]. Convincing the managers and physicians of the benefits of oral health and adequate oral health care as well as improving the oral health knowledge and oral health care attitude and skills of nurses and nurse aides may contribute to an improvement of oral health and quality of life of residents. Although during the last several years increasing attention has been paid to improving oral health care, there is still a need for guidelines and effective protocols, for oral health and oral hygiene assessment tools for nurses and nurse aides, and for teaching nurses and nurse aides practical skills of daily oral hygiene care [37-39]. In 2007, the Dutch guideline *"Oral health care in (residential) care homes for elderly people" *was developed and presented to all (residential) care homes for elderly people in The Netherlands and a part of Flanders, Belgium. The Dutch guideline is satisfying the Appraisal of Guidelines Research & Evaluation Instrument (AGREE) [40]. It describes all aspects of good oral health and oral health care, presents the methods and skills needed for providing oral health care to residents, and presents effective oral health and oral hygiene assessment tools. The ultimate objective of the guideline is to improve the oral health of the residents.

Any care guideline needs careful implementation as well as research for assessing its residents' and care providers' compliance. Guideline implementation involves the concrete activities and interventions undertaken to turn policies into desired results. Previous implementation research studies have revealed that implementation of a guideline is very complicated. Although numerous attempts have been made, an effective implementation method has not yet been discovered. Key factors are 'buying in' the care providers, determining during the implementation project which factors are stimulating or inhibiting the project, and determining the care providers' perceived barriers and compliance [41-48].

### Scientific hypothesis

The scientific hypothesis of the present study is that supervised implementation of the guideline "*Oral health care in (residential) care homes for elderly people*" is more effective in improving oral health and oral health care of the residents when compared to non-supervised implementation.

### Aim and objectives

The overall aim of the study is to compare a supervised versus a non-supervised implementation of the guideline "*Oral health care in (residential) care homes for elderly people"*. The aim can be rendered into 5 research questions:

1. Is there any statistically significant difference between oral hygiene levels of elderly residents in (residential) care homes with supervised implementation of the guideline when compared to those in (residential) care homes without supervised implementation of the guideline?

2. Is there at care home level any statistically significant difference between attitude and knowledge level of nurses and nurse aides of (residential) care homes with supervised implementation of the guideline when compared to those in (residential) care homes without supervised implementation of the guideline?

3. Is there any statistically significant difference in impact on the outcome variables of research questions 1 and 2 between the (residential) care homes in The Netherlands when compared to Flanders (Belgium) and which factors are causing the country differences?

4. Which factors are stimulating or inhibiting the implementation of the guideline in the (residential) care homes in The Netherlands and Flanders (Belgium)?

5. What is the compliance of and which barriers are perceived by the nurses and nurse aides in (residential) care homes in The Netherlands and Flanders (Belgium) while implementing the guideline?

## Methods/Design

### Design of the study

The study is a cluster randomized intervention trial with an institution as the unit of randomization. A random sample of 12 (residential) care homes accommodating a total of 120-180 somatic as well as psycho-geriatric residents in The Netherlands as well as in Flanders (Belgium) are randomly allocated to an intervention or control group. Representative samples of 30 residents in each of the 24 (residential) care homes are monitored during a 6-months period. Research data are gathered at baseline and at 6 months after the start of the study. The study is supervised and monitored by 2 investigators, the first and second author of this article. In each institution, an institution study supervisor, appointed by the managing director, is responsible for executing all study activities. The intervention consists of supervised implementation of the guideline "*Oral health care (residential) care homes for elderly people*" and a daily oral health care protocol. This protocol is derived from the guideline and formulated by the authors. Primary outcome variable is the oral hygiene level of the participating residents. To determine the stimulating or inhibiting factors of the implementation project and the nurses' and nurse aides' compliance and perceived barriers, a process evaluation is carried out [49]. The study is conducted according to the principles of the Declaration of Helsinki (version 17c, 2004) and in accordance with the Medical Research Involving Human Subjects Act (WMO). The study protocol is approved by the Ethics Committees of the Ghent University, Belgium (OG017 - approval 2008/440) and the Radboud University Nijmegen, The Netherlands (NL24666.091.08 approval 2008/273).

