Based on previous studies, an intraclass correlation coefficient of 0.95 and a standard deviation (sd) for dental plaque and denture plaque of 0.75 and 0.88 respectively is used. A 25% improvement of oral hygiene level is the presumed effect of the intervention. With regard to the design effect and drop-outs, loss to follow up, and uncertainty in power calculation, a sample size of 360 residents and 12 clusters per country seems an achievable number for the 6-months period. This means 30 residents per (residential) care home.

To participate in the study, a resident should:

• Supply a written informed consent, undersigned by himself or his legal representative

• Have teeth and/or partial or complete dentures

• Have the cognitive and physical condition required for undergoing an oral examination

• Be residing in the institution during the entire 6-months period presumably.

Residents are excluded when in day-care, in short-term residency, in coma, in palliative care or terminally ill, using a denture adhesive, expressing verbal or physical resistiveness before or during an oral examination.

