#### Oral examination

The oral hygiene level of natural teeth is assessed using the validated plaque index described by Silness and Löe (score range 0-3) at a subset of the so-called 'Ramfjörd teeth' [50]. In absence of one of these teeth, the corresponding distal neighbour tooth will be assessed. The oral hygiene level of dentures is assessed using a Methylene Blue^® ^denture plaque disclosing solution according to the method of Augsburger and Elahi (score range 0-4) [51].

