### Statistical analysis

Both categorical and continuous variables are initially analyzed using exploratory data analysis, employing a variety of mostly graphical techniques and techniques for testing the necessary assumptions. The institution is the unit of randomization and the residents are the units of analysis. Cluster effects are addressed in the analysis. Intraclass correlation will be calculated for each outcome variable as a measure of correlation among residents within the institutions as well as among institutions within each country. The effect of the implementation project at individual, institution and country level is summarized and analyzed in a multilevel comparative analysis. Three comparative dimensions are handled simultaneously: the resident effect, the institution effect, and the country effect. Therefore, a three-level structure is used with resident (level 1) and institution (level 2), nested in broader organization units on country level (level 3). Differences in primary outcomes at baseline and differences between the intervention and the control group as well as between countries at baseline and at 6 month are calculated. Covariates at individual level are the subjects of the resident questionnaire and the nurse and nurse aide questionnaire.

Responses to the semi-structured interview of the process evaluation are analyzed using coding techniques commonly utilized for qualitative research methods [55]. Recurrent themes in the responses are used to set up a framework.

All research data are analyzed using MANOVA. A multilevel regression analysis is performed to determine the most important predicting factors with respect to oral hygiene level.

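### The single named primary outcome is two plaque indices in overlapping groups of residents, with no primary index and no rule for what answers research question 1

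*Protocol article*

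**What the plan says.** The Design of the study section of the protocol article names one outcome: "Primary outcome variable is the oral hygiene level of the participating residents". The Abstract and the Discussion keep the singular, and the sample-size text under Participants and setting also treats oral hygiene level as one measure with one standard deviation symbol.

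The Oral examination section defines two instruments:

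- "The oral hygiene level of natural teeth is assessed using the validated plaque index", scored 0 to 3.
- "The oral hygiene level of dentures is assessed using a Methylene Blue" disclosing method, with "score range 0-4".

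Table 1 puts both in one row, as the measure of the intervention effect. The resident criteria require a participant to "Have teeth and/or partial or complete dentures".

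The sample-size text gives two standard deviations, 0.75 for dental and 0.88 for denture plaque. Everything else appears once: ICC 0.95, a 25% improvement, 80% power, significance level 0.05, and 360 residents in 12 homes per country. "This means 30 residents per (residential) care home".

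The Statistical analysis section uses the plural, "Differences in primary outcomes at baseline". It plans a multilevel analysis with residents as units, and also says that MANOVA is applied to all research data. Research question 1 asks about a significant difference in oral hygiene levels and does not say on which index.

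**The concern.** The article disagrees with itself on whether there is one primary outcome or two. The two scores have different ranges and no rule adds or rescales them, so they are not one variable. An edentulous resident has no dental score, and a resident without a denture has no denture score.

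Two consequences follow. First, research question 1 can be answered on either index, and nothing fixes in advance which one, or whether both are needed. Tooth brushing and denture cleaning are different tasks, so a split result is plausible. As written, it could be presented as success or as failure after the data are seen. Second, the only joint method named does not fit the population that the eligibility criteria enrol.

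**Working it through.** **Inputs from the article:** one significance level, 0.05; power 80%; ICC 0.95; 30 residents per home; 24 homes; SDs 0.75 and 0.88; scales 0-3 and 0-4. **Not given:** sidedness, the mean of either index, the share of residents with teeth, dentures or both, and the correlation between the two test results. I assume two-sided tests and equal allocation.

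**1. The plan's own size.** 12 × 30 = 360 per country and 24 × 30 = 720 in total. The design effect is 1 + 29 × 0.95 = 28.55. The 360 cannot be rebuilt from the stated inputs. 360 / 28.55 = 12.6, or 6.3 effective residents per arm, which gives a detectable dental difference of 2.80 × 0.75 × √(2/6.3) = 1.18. As a 25% change this implies a mean of 1.18 / 0.25 = 4.73, above the scale maximum of 3. The denture index gives 1.39 and 5.55, above 4. That is a separate matter from this point. It matters here only because no per-index size can be checked.

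**2. False-positive rate, if the indices are tested separately at 0.05 and either counts.** The formula is 1 − P(|Z₁| ≤ 1.96 and |Z₂| ≤ 1.96), with the two test statistics bivariate normal.

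| Correlation of the tests | Familywise error |
|---|---|
| 0 | 1 − 0.95² = 9.75% |
| 0.3 | 9.5% |
| 0.5 | 9.1% |
| 0.8 | 7.8% |
| Upper bound, any correlation | 0.05 + 0.05 = 10% |

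If both indices had to succeed, the rate would be no higher than 5%. The article does not choose between these rules.

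**3. MANOVA against eligibility.** Let t and d be the shares of residents with a dental and a denture score. Every participant has at least one, so the share with both is t + d − 1. A standard MANOVA with the two indices as joint outcomes uses only that share. The article gives neither t nor d. For illustration only, if one index were scored in 40% of residents (12 of 30 per home), the other would be scored in at least 60%, and between 0 and 12 residents per home would have both. The rest, although eligible by design, would drop out of the joint test.

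**4. Does a smaller number per index cost precision on the plan's own inputs?** Effective n = 24m / [1 + (m − 1) × 0.95].

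- m = 30: 720 / 28.55 = 25.22
- m = 15: 360 / 14.30 = 25.17
- m = 12: 288 / 11.45 = 25.15

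The loss is under 1% (25.15 / 25.22 = 0.997).

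**5. Power at the first Holm step.** An effect with 80% power at two-sided 0.05 has a standardised size of 1.960 + 0.842 = 2.802. At two-sided 0.025 the critical value is 2.241. Power is Φ(2.802 − 2.241) = Φ(0.56) ≈ 71%.

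**The case against.** The strongest objection is that this is a condensed article. Multiplicity procedures and the reading of split results are commonly left to a statistical analysis plan or full protocol, neither of which is shown. That stands as far as the bare absence of a multiplicity rule goes. It does not cover what the article does state: one primary outcome in one section, two instruments for it in another, the plural in a third, and a joint method that its own eligibility criteria undercut.

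A reader might also infer more than the text supports:

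- **That each index is tested at 0.05, so the false-positive rate exceeds 5%.** The level is stated once, with no number of tests. MANOVA could be meant as a joint test, or both indices might be required to improve. The inflation in step 2 holds only for separate, unadjusted tests with either counting.
- **That the trial was sized as if all 30 residents per home had both scores.** Thirty is the only cluster size given and is not split by dentition, but no such assumption is written. The 360 is presented as achievable, after unquantified allowances.
- **That many residents have only one index, or that neither index reaches 30 per home.** The article has no dentition figures. The criteria show only that such residents are eligible.
- **That the effective sample size per index is materially overstated.** At the stated ICC of 0.95 it is not (step 4). A material loss needs a much smaller ICC, which is not the plan's figure.

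Holm is also not the only remedy. A single primary index, or a requirement that both succeed, would also close the gap.

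**Conclusion.** The concern holds in a limited form. The article does not settle what its primary outcome is: one name covers two indices on different scales in overlapping groups, with one significance level and no success rule. This leaves open two chances at the primary claim. If they are used without adjustment, the familywise error is between about 7.8% (correlation 0.8) and 9.75% (independence), with a ceiling of 10%. These figures rest on two-sided tests and on either index counting, which the article neither states nor rules out. That MANOVA would exclude residents with one score follows from the eligibility criteria for any analysis taking both indices as joint outcomes. The number lost cannot be given, because the dentition shares are not reported. No claim about lost sample size is made.

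**What to change.** State that there are two primary outcomes, dental plaque and denture plaque. Analyse each with the planned multilevel model, not MANOVA, in the residents who have that index. Test them by Holm at an overall two-sided 0.05: compare the smaller p-value with 0.025 and, if it passes, the larger with 0.05. Limit each conclusion to the index that passes, so that a split result has a defined meaning. Use the plural throughout, and word research question 1 to match.

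The change takes a few sentences and no extra data. Its price is power at the first step: about 71% for an effect sized for 80% at 0.05. Once one index passes, the other is tested at the full 0.05. Whether the trial reaches 80% for either index cannot be checked from the article, so the 71% is relative to that target.

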### Participants and setting

In each country, a sample of (residential) care homes for elderly people is obtained using stratified (geographical distribution) cluster sampling with replacement. A (residential) care home is considered eligible for inclusion unless any of the following exclusion criteria are applicable:

• The management of the institution does not agree with the random allocation to the intervention or control group;

• The institution has mainly wards accommodating less than 20 residents;

• The institution has only somatic or psycho-geriatric wards;

• An oral health care guideline or protocol has already been introduced and implemented;

• Nurses and nurse aides have received special training on oral health care during the last 24 months;

• More than 5 other major care innovation projects have been implemented during the last 24 months.

Once the managing director of an institution agrees to participate by written informed consent, the institution is randomly allocated to either the intervention group or the control group of the country. Based on the power calculation (see following indentation) a representative cohort of 30 residents of the institution needs to be included.

Crucial factors for calculating the sample size (n) are the presumed distribution of the outcome measure (oral hygiene level) in the population of residents (*σ*), the presumed effect of the intervention (*μ*^1 ^- *μ*^2^), the power required (1-*β*), the a priori determined level of significance (*α*), and the value of the intraclass correlation (design effect). An a priori power of 80% and a level of significance of 0.05 are predetermined. The design effect (Deff) represents the ratio of the number of residents required using cluster randomization to the number of residents required using individual randomization.

The primary formula for calculating the sample size is: .

Deff = 1 + [(m - 1) *ρ*]; m = the number of residents in each institution, *ρ *= the intraclass correlation coefficient.

The adjusted sample size (n^adj^) equals: n × Deff. The number of residents in each institution (m) = n^adj ^: k; k = the number of institutions in the sample.

Based on previous studies, an intraclass correlation coefficient of 0.95 and a standard deviation (sd) for dental plaque and denture plaque of 0.75 and 0.88 respectively is used. A 25% improvement of oral hygiene level is the presumed effect of the intervention. With regard to the design effect and drop-outs, loss to follow up, and uncertainty in power calculation, a sample size of 360 residents and 12 clusters per country seems an achievable number for the 6-months period. This means 30 residents per (residential) care home.

To participate in the study, a resident should:

• Supply a written informed consent, undersigned by himself or his legal representative

• Have teeth and/or partial or complete dentures

• Have the cognitive and physical condition required for undergoing an oral examination

• Be residing in the institution during the entire 6-months period presumably.

Residents are excluded when in day-care, in short-term residency, in coma, in palliative care or terminally ill, using a denture adhesive, expressing verbal or physical resistiveness before or during an oral examination.

